### Statistical analysis strategy

All statistical analyses will be performed using IBM SPSS Statistics for Windows, v.22.0 (IBM, Armonk, NY, USA). Data will be checked for normal distribution using the Shapiro-Wilk test. The primary endpoint measurement is myo-MPS. Secondary endpoints are leg lean mass (DXA), *rectus femoris* muscle thickness (ultrasound), muscle fibre CSA (immunohistochemistry) and quadriceps muscle strength (isokinetic dynamometry). All measurements will be analysed using a 2-way between and within mixed model ANCOVA with condition (ß-lactoglobulin vs. placebo) as the between-group factor and time period (basal *vs*. prehabilitation *vs.* immobilisation) as within-group factors. Diet and physical activity status will be input as covariates. Where appropriate (i.e. measurements of MPS, leg lean mass, muscle thickness and quadriceps muscle strength), a within-subject control (non-immobilised leg) will be applied to the statistical model when making between group comparisons. The key objective is to compare the effect of the intervention vs. placebo in an unpaired sample. We plan to make three comparisons between the two groups (Δ baseline to immobilisation, Δ prehabilitation to immobilisation, and Δ baseline to prehabilitation for all measurements), disregarding sex as a factor. There is a risk this may introduce type 2 error (rather than type 1 because the randomisation is granular), but we have no reason to anticipate that sex will be a significant confounder. Additional justification for this strategy is because we anticipate that the number of male and female participants will not be equal. The strategy will be to determine from the ANCOVA above whether the intervention is a significant source of variance for each of the primary and secondary endpoint measurements. Bonferroni post hoc testing will be undertaken only if *F* is significant (*P* < 0.05), and there is no variance in homogeneity. The post hoc test will be a *t* test but with an adjustment in the *P* value to accommodate the number of comparisons. The adjustment will be to add a degree of freedom for each of the comparisons. We consider this statistical approach optimal for permitting reliable discovery in a reasonable timeline. Statistical significance will be set an *α*-level of *P* < 0.05.

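### The post hoc rule is named Bonferroni but defined as adding degrees of freedom, which slightly loosens each test, and the F test that gates it is not identified

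*Protocol article*

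**What the plan says.** All of this stands in the protocol article, under Statistical analysis strategy.

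- **Family of comparisons.** "We plan to make three comparisons between the two groups": baseline to immobilisation, prehabilitation to immobilisation, and baseline to prehabilitation, for every measurement.
- **Gate.** The mixed ANCOVA is to show "whether the intervention is a significant source of variance for each of the primary and secondary endpoint measurements". Then: "Bonferroni post hoc testing will be undertaken only if *F* is significant (*P* < 0.05), and there is no variance in homogeneity".
- **Test and intent.** "The post hoc test will be a *t* test but with an adjustment in the *P* value to accommodate the number of comparisons".
- **Rule.** "The adjustment will be to add a degree of freedom for each of the comparisons".
- **Level.** "Statistical significance will be set an *α*-level of *P* < 0.05". Whether tests are one- or two-sided is not stated.

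The section nowhere mentions dividing alpha or multiplying P.

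**The concern.** Bonferroni for three comparisons means testing each at 0.05/3, or multiplying each P value by 3. Adding degrees of freedom does neither. More degrees of freedom thin the tails of the t distribution, so the same t statistic gets a smaller P value. The stated rule therefore works against the stated intent, and an analyst cannot follow both.

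Three things are at stake:

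1. **Labelling.** P values could be published as Bonferroni-adjusted when they are slightly more favourable than raw ones.
2. **The gate.** If the rule gives no correction, multiplicity control rests on the F gate alone. The three comparisons are differences in change, which is what the condition-by-time interaction tests. The text speaks only of the intervention as a source of variance, which could equally mean the condition main effect.
3. **Homogeneity.** The clause "and there is no variance in homogeneity", read in its evident sense, stops the post hoc contrasts between arms whenever variances differ. The article gives no alternative for that case.

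**Working it through.** The plan gives no numerical figure for the adjustment, so there is none to reproduce. The check compares the written rule with the method it names.

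**Inputs**
- 12 per group (Power calculation) and 1:1 allocation (Randomisation process). An unpaired t test has 12 + 12 - 2 = 22 df.
- Three comparisons and alpha 0.05 (Statistical analysis strategy).
- Assumptions: two-sided tests; covariates ignored in the df; all three extra degrees of freedom added to each test, giving 22 + 3 = 25.

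**1. Critical values and per-comparison error.** Error is P(|t| with 22 df > critical value).

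| Rule | Critical t | Per-comparison error |
|---|---|---|
| Unadjusted, 22 df | 2.074 | 5.00% |
| As written, 25 df | 2.060 | 5.15% |
| If losing 3 df was meant, 19 df | 2.093 | 4.81% |
| Bonferroni, 0.05/3 at 22 df | 2.591 | 1.67% |

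Neither direction of the df change comes near Bonferroni. Fewer residual df do not alter the picture: from 20 df, adding three moves the critical t from 2.086 to 2.069, a true error of 5.18%.

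**2. One P value.** A raw P of 0.040 (t = 2.183, 22 df) becomes 0.039 at 25 df. Bonferroni gives 3 x 0.040 = 0.12.

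**3. Family-wise error within one endpoint.** Simulation with 12 per arm, three periods, normal data with unit SD, and an equal between-period correlation of 0.3, 0.5 or 0.7 (assumed, because the protocol gives none); 100,000 replicates per setting. Group differences are listed as baseline / prehabilitation / immobilisation. Each entry is the chance of at least one false positive among the contrasts that are truly null.

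| Group differences (SD) | Rule | Interaction gate | Main-effect gate |
|---|---|---|---|
| 0 / 0 / 0 | as written | 4.9-5.0% | 0.6% |
| 0 / 0 / 0 | Bonferroni | 3.5% | 0.2% |
| 0 / 0 / 1.6 | as written | 5.1% | 1.4-2.0% |
| 0 / 1.6 / 1.6 | as written | 5.0-5.2% | 4.2-4.7% |
| 0 / 1.6 / 0 | as written | 5.1-5.2% | 1.5-2.1% |
| 1.5 / 1.5 / 1.5 | as written | 5.0-5.1% | 12.4-12.8% |
| 1.5 / 1.5 / 1.5 | Bonferroni | 3.5-3.6% | 4.4-4.5% |

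The interaction gate holds every pattern near 5%. With three periods, any two changes determine the third, so once one contrast is non-null at most one null contrast remains. The main-effect gate fails only when the arms differ by a constant amount at all periods: the gate then opens almost always (98% to nearly 100% of replicates), although every change contrast is null.

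**4. Cost in power.** For d = 1.6 and 12 per group the noncentrality is 1.6 x sqrt(12/2) = 3.92. Two-sided power at 22 df is 96% at alpha 0.05 and 90% at alpha 0.0167. This takes the protocol's d as applying to the contrast tested.

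**The case against.** The strongest defence is that the F gate already controls multiplicity. A gated set of pairwise contrasts among three means is a recognised procedure, and the interaction-gate results above bear this out. This stands.

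A reader might infer that the three comparisons go uncorrected and that the chance of a false positive per endpoint is about 12.7%. The documents do not support that. The figure is what the written cut-off gives with no gate (12.6-12.7% in the complete-null simulation), and the plan has one: "Bonferroni post hoc testing will be undertaken only if" F is significant. The article also states the intent to adjust P for the number of comparisons. The fault is a contradiction between that intent and the rule, and dropping the rule restores the intent.

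Two further points are fair. The loosening itself is tiny, 5.00% to 5.15%; the substance is the missing division by three. And the constant-offset case is not one that treatment should produce, because arms are randomised and baseline precedes supplementation. It shows why the gate should be named, and is not a forecast.

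A reader might also infer that a failed homogeneity check leaves the intervention untested. It does not: the ANCOVA tests it regardless. Only the post hoc contrasts would be blocked, and a fallback may exist in an analysis plan not shown.

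The defence does not rescue the sentence. It is a specific published instruction, it is wrong, and it conflicts with the method named just before it.

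**Conclusion.** The point holds as an internal contradiction with a wrong rule. Followed literally, it yields P values labelled Bonferroni that are slightly smaller than unadjusted ones, with per-comparison error of 5.15% where the label implies 1.67%. These figures assume two-sided tests, 22 df before the addition and three degrees of freedom added; with fewer residual df the direction is the same.

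Within an endpoint, family-wise error is near 5% if the gate is the interaction. It is no more than about 5% with a main-effect gate in the patterns examined with no baseline difference. It reaches about 12.6% only with a main-effect gate and a constant offset that includes baseline, against about 4.5% under Bonferroni. These rest on the simulation's normality and correlation assumptions. Because the plan does not say which F is the gate, the protection cannot be confirmed from the text.

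Severity: should-fix. The error lies in the wording and labelling of a secondary step, and inflation well beyond nominal needs an unlikely combination.

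**What to change.** 1. Delete the sentence on adding degrees of freedom. State instead that all three between-group change comparisons for an endpoint are adjusted by Bonferroni (P x 3, equivalently alpha 0.0167 each) or by Holm. The correction must cover all three: testing one at 0.05 and the other two at 0.0167 each, with no ordering, bounds family-wise error only at 0.05 + 2 x 0.0167 = 0.083.
2. Name the condition-by-time interaction as the F that gates the post hoc tests.
3. Replace the homogeneity condition with Welch (Satterthwaite) degrees of freedom when variances differ, so that the contrasts between arms are always reported.

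The cost is a few sentences, settled before unblinded analysis, and some less favourable P values. Gate and Bonferroni together are somewhat conservative (about 3.5% under the complete null). At d = 1.6 and 12 per group, power for a single contrast falls from about 96% to about 90%, still above the 0.8 the protocol set, so no change in sample size follows.

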## Discussion

Previous studies have reported mixed findings regarding the effectiveness of non-pharmacological prehabilitation strategies to mitigate impairments in MPS in response to short-term muscle disuse. For instance, McGlory et al. reported higher integrated rates of myo-MPS following 2 weeks of leg immobilisation when healthy, recreationally active females undertook a 6-week prehabilitation strategy of omega-3 fatty acid supplementation compared to a sunflower oil placebo control [20]. In contrast, thrice daily high dose (15 g/d) leucine supplementation during 7 days of leg immobilisation failed to mitigate the disuse-induced decline in myo-MPS in healthy young males [12]. Moreover, 7 days of resistance exercise prehabilitation failed to attenuate the decline in myo-MPS elicited by 5 days of inpatient bedrest in older adult males [27]. To date, studies of prehabilitation strategies conducted within the context of skeletal muscle disuse have primarily been unimodal in design, focussed on the independent effects of a nutritional intervention [10-12, 17] or exercise-based intervention [18, 27] alone. To our knowledge, the present study is novel in examining the efficacy of a bimodal prehabilitation strategy that combines ß-lactoglobulin supplementation and resistance exercise training in modulating muscle protein metabolism following a short-term period of muscle disuse. As proof-of-concept, we hypothesise that this complex, short-term, non-pharmacological prehabilitation intervention will diminish the decline in MPS induced by 5 days of leg immobilisation in physically-active young males and females. To translate these data into clinical practice, follow up studies in more compromised populations are warranted, including patients due to undergo hip or knee replacement surgery [10, 11].

## Trial status

Protocol version 1 dated 15 December 2022. Recruitment start date: 1 March 2023. Recruitment end date: January 10, 2024.

## Data Availability

Yes

## Abbreviations

1-RM: One-repetition maximum
ANCOVA: Analysis of covariance
AUC: Area under the curve
CSA: Cross-sectional area
DXA: Dual-energy x-ray absorptiometry
ISAK: International Society of Anthropometry and Kinanthropometry
MPS: Muscle protein synthesis
